## Abstract

**Background:**

Acquired brain injury (ABI) often leads to persisting somatic, cognitive, and social impairments. Cognitive impairments of processing speed, sustained attention, and working memory are frequently reported and may negatively affect activities of daily living and quality of life. Rehabilitation efforts aiming to retrain these cognitive functions have often consisted of computerized training programs. However, few studies have demonstrated effects that transfer beyond the trained tasks. There is a growing optimism regarding the potential usefulness of virtual reality (VR) in cognitive rehabilitation. The research literature is sparse, and existing studies are characterized by considerable methodological weaknesses. There is also a lack of knowledge about the acceptance and tolerability of VR as an intervention method for people with ABI. The present study aims to investigate whether playing a commercially available VR game is effective in training cognitive functions after ABI and to explore if the possible effects transfer into everyday functioning.

**Methods:**

One hundred participants (18–65 years), with a verified ABI, impairments of processing speed/attention, and/or working memory, and a minimum of 12 months post injury will be recruited. Participants with severe aphasia, apraxia, visual neglect, epilepsy, and severe mental illness will be excluded.

Participants will be randomized into two parallel groups: (1) an intervention group playing a commercial VR game taxing processing speed, working memory, and sustained attention; (2) an active control group receiving psychoeducation regarding compensatory strategies, and general cognitive training tasks such as crossword puzzles or sudoku. The intervention period is 5 weeks. The VR group will be asked to train at home for 30 min 5 days per week.

Each participant will be assessed at baseline with neuropsychological tests and questionnaires, after the end of the intervention (5 weeks), and 16 weeks after baseline. After the end of the intervention period, focus group interviews will be conducted with 10 of the participants in the intervention group, in order to investigate acceptance and tolerability of VR as a training method.

**Discussion:**

This study will contribute to improve understanding of how VR is tolerated and experienced by the ABI population. If proven effective, the study can contribute to new rehabilitation methods that persons with ABI can utilize in a home setting, after the post-acute rehabilitation has ended.

**Supplementary Information:**

The online version contains supplementary material available at 10.1186/s13063-024-08178-7.

## Introduction

### Background

Acquired brain injury (ABI) affects an estimated 200 per 100,000 of the global population [1], and represents a severe health issue which often leads to life-long somatic, cognitive, emotional and social impairments. Many persons with ABI need intensive, interdisciplinary rehabilitation efforts, both in the acute and chronic phase [2]. Cognitive impairments are frequently reported in the chronic phase [3] and may have a negative impact on many aspects of a person’s life, including activities of daily living, work attainment, and quality of life [4, 5].

Computerized cognitive training has gained much attention as a restorative strategy [6, 7], targeting impaired processing speed, working memory and sustained attention [8, 9]. Restorative techniques aim to alleviate the specific impaired cognitive function through massed training trials [10]. These interventions build on the rationale that specific exercises within specific cognitive domains lead to generalized effects to other tasks than those that are trained [11]. CogMed, Lumiosity and BrainHQ are well-known computerized training programs [11], consisting of variations of verbal and visuospatial memory span tasks [12].

Studies involving computerized cognitive rehabilitation research suggest some efficacy [9], but several methodological issues have been raised, such as small number of participants, lack of control groups and differences in training dosages. The major concern related to computerized training interventions is however the lack of ecological validity, i.e. relevance to everyday life [13]. Outcome measures have often mimicked training content, making the generalizability of effects impossible to evaluate. One extensive literature review and one meta-analysis concluded that to the degree that computerized cognitive training had any effects, these were only short term and did not generalize to everyday functioning [8, 12].

There is a growing optimism regarding the usefulness of virtual reality (VR) in cognitive training intervention. This is due to its capacity for providing contextualized environments that resemble everyday situations, and the possibility to high training volume over short periods of time, in safe environments [6]. VR provides a non-invasive, immersive, computer-generated three-dimensional environment, in which the task difficulty can be adjusted and individualized. VR allows the user to interact with virtual objects, via sensorimotor channels in a head-mounted display, while muting outside stimuli [14]. Compared to technologies where stimuli are displayed on a two-dimensional computer screen, VR greatly increases the sense of presence, through its capacity to realistically convey visual and auditory information [15]. The experience of being in a virtual environment [16] provides the patient with rich and contextualized stimuli and tasks that may resemble everyday cognitive challenges, which may increase motivation and engagement, and potentially promote generalization of treatment effects [17].

The development of specialized VR systems for cognitive rehabilitation to ensure ecologically valid cognitive exercise tasks are called for [18, 19]. At present, few such options exist. In addition, specialized games developed for rehabilitation purposes often resemble cognitive tests and gamification aspects are less emphasized. Commercially available VR games, on the other hand, apply elements from gamification theory [20] that enhance motivation, such as clearly stated goals, salient rewards and adjustable difficulty levels, factors that are known to predict favorable outcomes following cognitive training [21]. As a result, research suggests that commercial video games may be as effective in improving attention as games created for rehabilitation [22].

A relatively recent review of VR interventions in cognitive rehabilitation after ABI identified only 13 studies [16]. While most of them concluded that VR was an effective method for training attention, memory, and problem-solving, scrutiny revealed severe methodological challenges. Only half of the studies involved immersive VR [23–28], while the rest used video games played on a screen. All studies utilizing immersive VR were published previous to the first generation of the VR systems that are in use today, rendering the technology non-comparable. Furthermore, small sample sizes were the norm and several studies were single case studies or lacked control groups [19]. Importantly, none investigated the effect of playing commercial VR games. There is thus a need for well-controlled randomized trials exploring the effectiveness of VR interventions in cognitive rehabilitation after ABI, and possible transfer effects to everyday activities [29].

Motivating effects of VR for healthy people are well established [30]. Our clinical experience, and the preliminary existing literature, indicates that most patients find it motivating to use VR for training purposes as well and tolerate it without major adverse effects. Cybersickness and fatigue are potential side effects of VR, particularly after extended use [31]. Cybersickness is similar to motion sickness, and it is not known if persons with ABI are more susceptible to these adverse effects, or if VR may exacerbate pre-existing symptoms in some individuals. To our knowledge, the only study reporting adverse effects of VR in an ABI population found that the technology was well tolerated by 18 of 21 patients [27], and that those who were not able to complete the training experienced “fatigue and frustration.” Furthermore, there are likely individual differences, both related to injury and other factors, when it comes to who might benefit from VR in rehabilitation. This has however not been systematically investigated.

### Aims and hypotheses

The primary aim of this study is:

To evaluate the effect of playing a commercial VR game as a means of re-training of processing speed, working memory, and sustained attention in persons in the chronic phase of acquired brain injury.

Secondary aims are to explore:Transfer effects to everyday functioning.How ABI patients experience using VR.How fatigue, motivation and presence is affected by VR training.

We hypothesize that the intervention group will demonstrate improved processing speed, working memory, and sustained attention compared to an active control group.

We furthermore hypothesize to find generalization of VR treatment effects to improved everyday functioning. Finally, we anticipate that the majority of patients with ABI will tolerate the use of VR well, and find the method motivating, but that a minority will experience adverse effects.

## Methods

### Study design

The study will be conducted as a two parallel-group exploratory randomized controlled trial (RCT) with an active control group. Participants will be randomized into either VR training or a control group, after baseline assessment, with an allocation ratio at 1:1 (Fig. 1). During the intervention period, participants in both groups will be followed up with a ten-minute phone call once per week, with standardized questions to each of the study conditions. This aims to increase fidelity and adherence to protocol, and adverse events will be monitored. For the participants in the intervention group, the phone call will also include technical issues if needed, and assessment of sense of presence (Multi-Modal Presence Scale [32]) during the intervention. Participants in both groups will answer weekly questionnaires regarding motivation (Situational Motivation Scale [33]) and fatigue (Fatigue Severity Scale [34]).

**Fig. 1 Fig1:**
[figure not shown]
Overview of study design

The primary and secondary outcome measures will be re-administered at the end of the 5-week intervention period (T2) and 16 weeks (T3) after baseline. After T3, the first ten participants from the VR group will be asked to take part in individual qualitative interviews to gain in-depth understanding of their experience with the use of VR as a training method and participation in the intervention.

The RCT will follow the CONSORT statement [35] and is registered in ClinicalTrials.gov (NCT05443542) and Open Science Framework (osf.io/6gphy). When preparing this protocol, we used the SPIRIT reporting guidelines and the SPIRIT checklist is available as an additional file (Additional file 1).

### Study setting

T1 (week 0), T2 (week 5), and T3 (week 16) assessments will be performed at Sunnaas Rehabilitation Hospital, the largest rehabilitation hospital in Norway and the owner of the study. Participants will receive tutorials on the use of the VR technology at baseline, and the interventions will be carried out in the participant’s homes (Fig. 2).

**Fig. 2 Fig2:**
[figure not shown]
Standard protocol items: recommendations for intervention trials (SPIRIT)

### Participants

Patients with ABI who have been admitted to Sunnaas Rehabilitation Hospital will be considered for inclusion, and screened for eligibility. Eligible participants will receive a letter with an invitation to participate in the study. If participants have not responded to the letter within fourteen days, the project members will call them and ask whether they are interested in participating. A next of kin nominated by the patient will be included to obtain comparative information on the participants’ everyday functioning.

#### Eligibility criteria

Inclusion criteria:Patients with ABI (traumatic brain injury, cerebrovascular incidents, anoxia, encephalitis, and non-progressive brain tumors)At least 12 months post injuryAged 18–65 yearsObjective or subjective impairments of processing speed, working memory, or sustained attention◦Objectively determined via neuropsychological assessments of processing speed, working memory, and sustained attention documented in medical journal◦Subjectively determined through a screening interview that include open-ended questions about perceived everyday processing speed, attention and working memory. The interview also contains the two items for attention and processing speed in the Rivermead Concussion Symptoms Questionnaire.Participants need to:◦Be physically able to operate VR equipment◦Understand instructions in Norwegian or English◦Be able to provide informed consent

Exclusion criteria:Aphasia affecting the ability to understand instructionsApraxia affecting the ability to operate the VR equipmentVisual neglectPhotosensitive epilepsySevere mental illness or active substance use disorderComorbid neurological disorders

### Descriptive and outcome measures

All outcome measures will be administered at T1, T2, and T3. The primary outcome is sustained attention and will be measured by the coefficient of variation (CoV) on the Conners Continuous Performance Test 3rd (CPT 3) [36]. Secondary outcomes are CPT 3, Mean hit Reaction time, Weschler Adult Intelligence Scale IV, Backwards Digit Span and Digit Sequencing [37], and patient competency rating scale [38]. Psychometric properties for each measure are acceptable. See Table 1 for an overview of all primary and secondary outcome measures, citations for psychometric properties, respondents, and time points.

**Table 1 Tab1:** Outcome measures, respondents and time points

*Outcome domain*	*Measure*	*Respondent*	*Time point*
**Sustained attention**	Conners Continuous Performance Test 3rd, coefficient of variation [39]	All participants	T1, T2, T3
**Processing speed**	Conners Continuous Performance Test 3rd, Mean hit Reaction time [39]	All participants	T1, T2, T3
**Working memory**	Weschler Adult Intelligence Scale IV, Backwards Digit Span and Digit Sequencing [40]	All participants	T1, T2, T3
**Everyday functioning**	Behavior Rated Inventory of Executive Functioning – Adult, working memory scale	All participants and next of kin	T1, T2, T3
	Patient Competency Rating Scale [38]	All participants	T1, T2, T3
**Motivation**	Situational Motivation Scale [41]	All participants	Weekly during intervention period
**Fatigue**	Fatigue severity scale [34]	All participants	Weekly during intervention period
**Cybersickness**	Simulator sickness questionnaire	Participants in VR group	Weekly during intervention period
**Sense of presence**	Multi-Modal Presence Scale [32]	Participants in VR group	Weekly during intervention period

At baseline (T1), neuropsychological test measures and questionnaires will be used for descriptive purposes. The following neuropsychological test battery will be applied: the Trail Making Test 4 (shifting) and subtest 3 of the Color Word Interference Test (inhibition) from the Delis-Kaplan Executive Function System test battery [42]. Abstract reasoning will be measured with Similarities and Matrices from WAIS IV [37]. Furthermore, we will include Coding from the WAIS IV as a measure of processing speed [37]. Immersive tendencies questionnaire will be administered at baseline to assess personality traits that may impact the level of experienced immersion [43].

Demographic data such as marital status, length and type of education and work status, will be gathered. In addition, injury-related data such as type and localization of injury will be collected.

### Randomization and allocation concealment

After the baseline assessment, the participants will be randomized into either the intervention or the control group. The randomization sequence will be generated electronically by an independent statistician, using block randomization [44] with a 1:1 ratio. Participants will be randomized after baseline assessment. The allocation sequence will be stored in a database that can only be accessed by the study’s principal investigator. Allocation will not be modified if the participant do not tolerate the intervention.

Blinding of participants and the researchers carrying out the intervention is impossible, but outcomes will be assessed by blinded assessors. Participants will be instructed to not reveal their group allocation to the outcome assessors. Data analysis will also be blinded as fake ID numbers will be assigned in the final database.

The personnel conducting the blinded assessments of the participants, will be trained by the research team to ensure data quality.

### Study interventions

#### Virtual reality

The experimental intervention is playing a commercially available VR game 30 min per day, for 5 weeks. The game selected is BeatSaber [45], which is a rhythm-based VR game that requires the player to react to colored blocks presented at the rhythm beats. As the game progresses the requirements of the game increases as the blocks are presented faster thus taxing both processing speed, sustained attention, and working memory. In addition to its cognitive requirements, the game was chosen due to availability on different platforms, which may ease implementation. It also has many users globally, securing the availability of the game in the future. The participants will be provided with a VR headset in order to conduct the VR training sessions at home. Throughout the intervention period they will have access to support, either by phone or video conference. Each 30-min session will be scheduled individually, with the instruction to use an alarm system to keep track of time. There are no existing clinical guidelines regarding recommended dosage and intensity of VR training; thus, the session length is based on clinical experience at SRH.

The VR game tracks the actual time each participant has spent playing the game during the intervention period. The amount of time spent playing will be recorded and used as a measure of intervention adherence.

#### Control group

An information booklet has been developed based on best practice evidence with information regarding compensatory strategies that participants can easily practice in their everyday lives. In addition to strategies, the booklet includes general information on topics that can affect cognitive functioning; national recommendation of physical exercise and physical activity, leisure activities (crossword puzzles, Sudoku, games and reading), sleep and nutrition. The control group will not be given a specific dosage; however, they will be encouraged to choose one or two topics to focus on during the intervention period. The control group will receive the same amount of therapist follow-up as the intervention group. The intervention group will not receive the information booklet.

At the end of the data collection period, the participants allocated to the control group will be offered to utilize VR as a method of training for a 5-week period. They will be given the possibility of the same amount of training and tutoring as the intervention group.

### Qualitative data collection

To investigate the participant’s experiences with VR as a method of cognitive training, semi-structured interviews will be conducted. An interview guide has been developed as recommended by Creswell [46], based on the acceptability framework developed by Sekhon and colleagues [47]. This includes questions regarding how participants feel about the intervention, the perceived amount of effort required to partake in the intervention, to what extent the participants understood the intervention, whether the participants perceived the intervention to result in its intended purpose, and the participant’s own belief that they can participate in the intervention. Interviews will be transcribed verbatim after each interview.

A pilot interview with one participant with previous experience with utilizing VR will be performed. After this an evaluation of the interview guide will be performed to assess whether amendments to the interview guide is needed.

### Technical solutions and data management

The intervention will be provided using the Oculus Quest 2 (Facebook Technologies, LLC). The Oculus Quest 2 is a wireless standalone VR headset that delivers the commercial VR game to the participants, creating the virtual environment through visual and auditory stimuli. The VR headset utilizes two motion-controlled hand controls that detect the hand movements of the participants in the virtual environment and provide haptic stimuli to the user. Oculus Quest 2 requires Meta accounts to set up the headset and to download and play the VR games. We will set up 20 Meta accounts, one for each headset.

Questionnaire data will be gathered using the University of Oslo’s solution for managing data, Services for Sensitive Data [48]. The TSD is an IT platform with a secure server that is approved for storing sensitive data for research purposes [48]. Questionnaires will be set up electronically using Nettskjema, which is a tool for designing and conducting online surveys [49].

All physical forms and test results will be kept in a locked cabinet. All data material will be recorded with the participant ID and will be de-identified. Only the researchers working on the project will have access to the list that connects participant IDs with names. Data will be stored electronically on a secure research server at SRH and will be deleted 5 years after the project period has ended. Only the research team will have access to the final trial dataset. Access to data is regulated by Norwegian laws regarding data protection and research ethics, and distribution of data is prohibited.

### Statistical analyses

Descriptive statistics will be performed to describe demographics, cognitive functioning and injury severity. Effect analysis of primary and secondary outcomes will be performed according to intention-to-treat analysis using data from all randomized participants, regardless of whether they complete the intervention. To determine changes in continuous outcome measures over time (T1, T2, and T3) between the groups, linear mixed-effects models will be used. Time and time-by-group interaction will be used as fixed effects and their interactions as indicators of the intervention effect. The main effect of group will be removed from the models to adjust for potential baseline differences [50]. In the same manner, we aim to explore associations between motivation, cybersickness, fatigue and sense of presence and interaction with time within the mixed-model framework. Estimated mean between group changes from baseline to T2 and T3 with 95% confidence intervals will be provided. For all outcomes, an alpha level of *p* = 0.05 will be applied.

Sub-group analyses of i.e. differences in duration since injury, age, and educational levels will be performed. Differences in continuous variables between groups will be tested using an independent sample *t*-test for normally distributed data, or by the Mann–Whitney *U* test for very skewed data. Linear regression analysis will be performed with registered adherence data as a possible predictor of treatment efficacy.

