### Sample size and power calculation

Comparable studies to guide a potential anticipated effect for power calculation are lacking. However, similar studies investigating the outcome of attention utilizing computerized gaming interventions report within-group improvement scaling from one to two standard deviations [51]. In addition, a cross-sectional study investigating a similar population at two time points with the same outcome measures was also utilized [52]. The sample size was calculated based on the coefficient of variation (CoV) of CPT as the primary outcome. A mean difference in change in CoV of CPT of 3% between baseline and follow up between the groups was defined as a clinically important difference. With equal allocation to both treatment groups and with an SD of 5%, power of 80%, and a significance level of 5%, the sample size was calculated to be 45 patients in each group. Allowing for 10% drop out, we aim to include a total of 100 patients.

The sample for qualitative interviews will be selected using selective sampling, meaning selecting individuals who are knowledgeable about the intervention or phenomenon being studied [53]. In this study, the sample will be the first ten participants that finish the VR intervention period.

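### The primary outcome has no primary time point: the trial is sized for one 5% comparison of CoV change, but the analysis gives two (T2 and T3), each at 0.05

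*Protocol article*

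**What the plan says.** Four parts of the protocol article bear on this.

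- **Descriptive and outcome measures.** CoV on the CPT 3 is the sole primary outcome. The measures of the other two cognitive domains are secondary: "Secondary outcomes are CPT 3, Mean hit Reaction time, Weschler Adult Intelligence Scale IV, Backwards Digit Span and Digit Sequencing". On timing, the section says only "All outcome measures will be administered at T1, T2, and T3". No visit is marked as primary.
- **Statistical analyses.** A linear mixed model covers T1, T2 and T3, and the time-by-group interactions are read as the intervention effect. Then: "Estimated mean between group changes from baseline to T2 and T3 with 95% confidence intervals will be provided". The significance rule is general: "For all outcomes, an alpha level of" 0.05 is used.
- **Sample size and power calculation.** The clinically important difference is "A mean difference in change in CoV of CPT of 3% between baseline and follow up between the groups". With an SD of 5%, 80% power and a 5% significance level, this gives 45 per group, and 100 in total after 10% dropout. The follow-up is not identified as T2 (week 5) or T3 (week 16).
- **Aims and hypotheses.** The main hypothesis is wider than the primary outcome: "We hypothesize that the intervention group will demonstrate improved processing speed, working memory, and sustained attention compared to an active control group".

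The Study design section labels the trial exploratory.

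**The concern.** The power statement describes one test and the analysis section produces two on the same outcome. Nothing links them, so the contrast that decides the trial is not fixed.

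The two visits answer different questions: T2 measures the effect at the end of training, T3 its persistence 11 weeks later. The distinction matters here, because the Introduction criticises earlier computerized training for effects that did not last. A difference at T2 alone and a difference at T3 alone would be read quite differently, yet under the present text either could be presented as the primary result once the data are known. In that case the 5% level used for the sample size would no longer describe the chance of a false claim on CoV.

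**Working it through.** **Inputs.** From Sample size and power calculation: difference in change 3, SD 5, power 80%, significance level 5%, equal allocation, 10% dropout. From Statistical analyses: two between-group contrasts per outcome (change to T2 and change to T3), alpha 0.05. The protocol gives neither the sidedness of the test nor the correlation between the two contrasts.

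**1. Reproduce the stated sample size.** Normal approximation for one two-sided test:

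n per group = 2 × SD² × (z₀.₉₇₅ + z₀.₈₀)² / δ² = 2 × 25 × (1.960 + 0.842)² / 9 = 43.6, rounded up to 44.

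The exact noncentral t calculation gives 79.5% power at 44 and 80.4% at 45, hence 45. A one-sided 5% test would need only 35, so the stated figure is two-sided. Dropout: 45 / 0.90 = 50 per group, 100 in total. The protocol's figures are correct for one comparison.

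**2. False-positive rate if either visit may count.** With independent contrasts: 1 − (1 − 0.05)² = 9.75%. The two contrasts come from the same patients and the same baseline, so a positive correlation ρ is expected. The error is then 1 − P(|Z₁| ≤ 1.96 and |Z₂| ≤ 1.96) for a bivariate normal pair, simulated with 1,000,000 draws:

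| Assumed ρ | Chance of at least one false claim on CoV |
|---|---|
| 0 (exact) | 9.75% |
| 0.5 | about 9.1% |
| 0.7 | about 8.3% |
| 0.8 | about 7.8% |
| 0.9 | about 7.0% |

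Every value exceeds 5%.

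**3. Rules that would hold 5%.** One joint test of the two time-by-group terms at 0.05 holds 5%. So does requiring significance at both visits, but at a price in power. If the difference of 3 is present at both visits, power lies between 0.804 × 0.804 = 64.6% (independent contrasts) and 80.4% (perfectly correlated contrasts). Neither rule appears in the text.

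**4. Cost of keeping both visits co-equal.** With 0.025 for each: n = 2 × 25 × (2.241 + 0.842)² / 9 = 52.8, so 53 per group, or 55 by the exact t. After dropout, 53 / 0.90 gives 59 and 55 / 0.90 gives 62 per group, that is 118 to 124 in total. If 45 per group is kept, power per contrast falls to about 73% (normal) or 71% (exact t).

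**5. Cost of naming one visit.** Alpha stays at 0.05, so step 1 applies unchanged: 45 per group, 100 in total.

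**The case against.** **The plan reports estimates; it does not declare an either-visit rule.** This is fair. Providing estimates with confidence intervals is a reporting commitment, and the interaction named as the effect could be tested jointly. A reader might infer that the 5% error rate is definitely lost. The text does not support that, because it does not say which decision rule is meant. What stands is that 5% is not secured.

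**The hypothesis covers three domains, so the problem may look much larger.** A reader might count three domains at two visits and arrive at 1 − 0.95⁶ = 26.5%, or require all three domains and compute 0.8³ = 51% power. Neither follows from the protocol. CoV is the only primary outcome and the sample size rests on it alone. Secondary tests at 0.05 do not inflate the error of a single named primary outcome, and no rule says that any one domain, or all three, decides the trial. The 51% would also assume 80% power for two outcomes that have no stated effect size or SD. What remains is a mismatch in wording between the hypothesis and the primary outcome. Likewise, the in-text list of secondary outcomes omits the BRIEF-A scale shown in Table 1, but this has no bearing on the primary error rate.

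**The trial is labelled exploratory.** This lowers the severity. It does not remove the ambiguity, because the same article sets a clinically important difference, 80% power and a 5% level for a named primary outcome, and anticipates conclusions about effectiveness.

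**Such detail may sit in an analysis plan that is not shown.** That holds for the handling of secondary outcomes. The point here rests on text that is present: one unspecified follow-up in the sample-size section against two contrasts at 0.05 in the analysis section.

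**Conclusion.** The point holds for the time point of the primary outcome. The protocol fixes CoV as primary and sizes the trial for one two-sided 5% comparison, but leaves open whether that comparison is at T2, at T3 or joint. Under an either-visit reading, the false-positive rate on CoV is roughly 7% to 10% instead of 5%. That range rests on two assumptions: that a significant result at either visit would be accepted as success, and that the correlation between the contrasts lies between 0 and 0.9. Under a joint test or a both-visits rule the error would be held, though the stated 80% power would not carry over automatically. The defect is moderate in size, but it concerns the trial's main conclusion and can be removed with a few words.

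**What to change.** Before unblinding, in the analysis section and the registrations:

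1. Name one primary CoV contrast at two-sided 0.05. This can be the between-group difference in change from T1 to one stated visit (for example T2, the end of the intervention) or one joint time-by-group test. The choice belongs to the sponsor, since no passage favours either visit.
2. Say in the sample-size section that the power statement refers to that contrast. If the joint test is chosen, check its power separately, because the present calculation is for a single contrast.
3. Make the other visit secondary, for example tested only if the primary contrast is significant.
4. State that the primary conclusion rests on CoV alone, with processing speed, working memory and everyday functioning as secondary or exploratory, and word the hypothesis to match.

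This takes a few sentences. With one visit named, the total stays at 100 and no further data are needed. The downside is that an isolated result at the other visit can no longer be claimed as the primary result.
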